#### Study outcomes

Our primary outcome is the adherence rates among MDR-TB patients on self-administered therapy vs DOT. Our secondary outcomes include (1) drug concentrations and adherence data for patients on self-administered therapy vs DOT; (2) proportion of patients with sputum conversion at 2, 8 and 11 months in each study arm; and (3) MDR-TB treatment outcomes (cure, treatment completion, loss to follow-up or death) by study arm.

### Sample size

Based on records from the NTP, treatment success rate for MDR-TB is 77.9%; from clinical trials, adequate adherence has been defined as 76–80% adherence rate; and from a meta-analysis, it has shown that 70% of patients on MDR-TB therapy are adherent [14, 15]. Our sample size calculation assumed that the adherence rate for the patients using MEMS technology is ≥ 70%, with study power of 0.9, precision of 0.05, and 20% loss to follow-up rate. We therefore require a sample size of 164 patients (82 in each arm) to demonstrate a 19% increment in MDR-TB treatment success. The intervention (MEMS technology) approach is considered non-inferior (19%) to the control (DOT) approach if the lower limit of the 95%CI of the difference between the two groups (i.e. MEMS group minus DOT group) is > −10%.

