## Trial design

This study will be conducted as a multi-centre open-label randomized clinical trial with two parallel arms and 1:1 enrolment ratio (82 patients in the intervention arm and 82 controls). We shall enrol a total of 164 participants newly diagnosed with pulmonary MDR-TB or rifampicin-resistant TB (RR-TB) from 3 TB tertiary care centres from 2 regions of the country.

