### Statistical: outcomes

#### Adherence assessment

The primary outcome is the overall adherence rates among MDR-TB patients on self-administered therapy and on DOT. For the participants on the intervention arm, opening of the devices will be equated to a patient swallowing their medication and adherence will be derived from the number of days the device was opened as a proportion of the total number of days in the entire period of their MDR-TB treatment. Patients on the intervention arm will be required to take no less than 70% of their medication to be considered as having good adherence. For participants on the control arm (DOT), adherence information will be obtained from their TB treatment cards. Adherence rates will be calculated from the number of days that they report to the DOTS facility as a proportion of the total number of treatment complaint days in the entire period of their MDR-TB treatment. Participants who take their medication at least 80% of the time (missing no more than 5 days each month) will be considered as having good adherence.

The primary analysis will be a comparison of overall adherence in each arm. Adherence by self-administration (proportion of expected openings of the MEMS devices) and DOT (proportion of DOT visits) will also be compared at 2 months and 6 months in the intervention and control arms. The chi-square test and 1-way analysis of variance models will be used to compare outcomes by randomization arm. We shall use independent samples *t*-test to test for statistical difference mean adherence rates in the patient in the intervention and control arms. We will use an intent-to-treat approach (analysed all participants regardless of drug refills) to compare adherence outcomes by randomization arm using a generalized estimating equations model using repeated measures with identity link, exchangeable correlation structure and robust variance estimates.

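### The sample-size paragraph ties 164 patients and 90% power to a 19% figure, but the decision rule uses −10 points, for which the stated inputs give about 24–34% power on the proportion-adherent scale

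*Protocol article*

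**What the plan says.** The Sample size section of the protocol article cites a 77.9% treatment success rate from programme records and a meta-analytic figure of 70% of patients adherent. It assumes adherence of at least 70% in the MEMS arm, "with study power of 0.9, precision of 0.05, and 20% loss to follow-up rate". It then concludes: "We therefore require a sample size of 164 patients (82 in each arm) to demonstrate a 19% increment in MDR-TB treatment success". The following sentence gives the decision rule. The MEMS approach is "considered non-inferior (19%) to the control (DOT) approach if the lower limit of the 95%CI" of MEMS minus DOT lies above −10%.

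Trial design confirms "two parallel arms and 1:1 enrolment ratio (82 patients in the intervention arm and 82 controls". Specific objectives makes non-inferiority on adherence the primary objective, and Study outcomes lists treatment outcomes as secondary. Adherence assessment states: "The primary outcome is the overall adherence rates among MDR-TB patients on self-administered therapy and on DOT". It derives adherence as a proportion of days and plans a chi-square test, a t-test on means and an identity-link GEE model.

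**The concern.** Two consecutive sentences give two magnitudes (19 and 10), two kinds of hypothesis (an increase, and non-inferiority) and two endpoints (treatment success, and adherence). The sample size and its 90% power are attached to the 19% figure. The trial will be judged on the 10-point figure.

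A margin enters a sample-size formula squared. Moving from 19 to 10 points multiplies the required number by (19/10)² = 3.61, other things equal. The trial could therefore be far less likely to show non-inferiority than its readers and its monitoring board are told. The figure printed beside the word non-inferior also leaves the margin less clear than it should be in an open-label trial.

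**Working it through.** **Inputs, all from the Sample size section:** 82 per arm; power 0.90; 0.05, called precision, with sidedness not stated; 20% loss; candidate rates 70% and 77.9%; figures of 19 and 10 points; a 95% CI for the decision. A two-sided 95% CI corresponds to one-sided 0.025. With 20% loss, 82 × 0.8 = 65.6, so about 66 evaluable per arm.

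**Step 1: where 82 could come from.** For non-inferiority of two proportions with equal true rates p and margin m,

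n per arm = (z_α + z_β)² × 2p(1−p) / m².

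- p = 0.779, m = 0.19, one-sided 5%, 90% power: (1.645 + 1.282)² × 0.3443 / 0.0361 = 81.7, so 82. This matches, but with no inflation for loss; 81.7/0.8 = 102.1.
- p = 0.70, m = 0.19, one-sided 5%: 99.6.
- p = 0.779, m = 0.19, one-sided 2.5%: 100.2.
- p = 0.70, m = 0.19, one-sided 2.5%: 122.2.
- Superiority, 70% vs 89%, two-sided 5%, 90% power: 89.6 (unpooled variance).

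Only the first of these gives 82.

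**Step 2: size needed for the −10-point rule** (one-sided 2.5%, 90% power, before loss).

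- p = 0.70: (1.960 + 1.282)² × 0.42 / 0.01 = 441.3, so 442 per arm.
- p = 0.779: (1.960 + 1.282)² × 0.3443 / 0.01 = 361.8, so 362 per arm.

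**Step 3: power of the planned size under the −10-point rule.** SE = √(2p(1−p)/n); power = Φ(0.10/SE − 1.96); half-width = 1.96 × SE.

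| p, both arms | n per arm | SE | 0.10/SE − 1.96 | Power | 95% CI half-width |
|---|---|---|---|---|---|
| 0.70 | 82 | 0.0716 | −0.563 | 28.7% | 14.0 points |
| 0.70 | 66 | 0.0798 | −0.706 | 24.0% | 15.6 points |
| 0.779 | 82 | 0.0648 | −0.417 | 33.8% | 12.7 points |
| 0.779 | 66 | 0.0722 | −0.576 | 28.2% | 14.2 points |

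At these rates the half-width exceeds 10 points, so equal observed proportions would not meet the rule.

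**Step 4: sensitivity.**

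- One-sided 5% instead of 2.5%: 35–46% over the same four cases.
- 90% adherent in both arms: 57% (82 per arm) or 48% (66 per arm).
- MEMS truly better, 75% vs 70%: 58% or 49%.
- MEMS truly better by 19 points, 89% vs 70%: about 99% or more at either size.

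**Step 5: the mean scale.** If the endpoint is mean percentage of days adherent, 90% power at −10 points with equal means requires SD ≤ 10 / ((1.960 + 1.282) × √(2/n)). That is 17.7 points for n = 66 and 19.8 for n = 82. The article gives no SD. For assumed values, power at 66 and 82 per arm is 97% and 99% (SD 15), 82% and 89% (SD 20), 63% and 73% (SD 25), and 48% and 57% (SD 30).

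**The case against.** The strongest reply concerns the scale. Adherence assessment derives adherence as a share of days and plans a t-test on means, so the primary comparison may be of mean percentages. Step 5 shows that power could then be adequate. This stands, and it is why the 24–34% must carry its condition. It does not rescue the 90% claim: the sizing paragraph works with a proportion of patients who are adherent, Adherence assessment also sets good-adherence cut-offs and a chi-square test, and no SD is given.

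The article also assumes MEMS adherence of at least 70%, which is a floor. Higher adherence, or a true MEMS advantage, raises power (Step 4). That is correct, but the Sample size section states neither as the basis for the non-inferiority rule, and at 90% in both arms power is still only 48–57%.

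The 66 per arm is a lower bound. Retention of study participants says withdrawn participants will be replaced, and Interventions: modifications says they may be. Replacement need not cover every loss, so 66 and 82 bracket the likely number.

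Four stronger readings may tempt a reader, and the document does not support them:

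- **That 164 fits only one derivation, so the 20% loss was certainly omitted.** The match in Step 1 is reverse-engineered: it uses the treatment-success rate and a one-sided 5% level that is not stated. Other routes reach about the same number at 80% power, for example 75%, 19 points, one-sided 5%, with loss included: 65/0.8 = 81.25, so 82. They depart from the stated "study power of 0.9", but they show that the derivation cannot be known.
- **That identical observed arms must fail.** This holds only on the binary scale, below about 88% adherence at 82 per arm or about 90.5% at 66 per arm.
- **That an inconclusive result is close to guaranteed.** A 24–34% chance of success contradicts that, and so does Step 5 if the SD is small.
- **That the sponsor could adopt a 19-point margin later.** The operative rule names only −10 points. The stray 19% is an ambiguity to remove and says nothing about intent.

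**Conclusion.** The contradiction is on the page and does not depend on how 164 was obtained. The Sample size section justifies the number by a 19% gain in a secondary outcome, while the primary rule is −10 points on adherence. The stated inputs do not deliver 90% power for that rule.

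For a binary endpoint, equal true rates of 70–77.9% and a two-sided 95% CI, power is 28.7–33.8% with 82 per arm and 24.0–28.2% with 66. On the mean scale, power is undetermined because no SD is stated. The conclusion is that the stated power is unsupported as written and needs correcting before the primary analysis. It does not follow that the trial is bound to fail.

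**What to change.** Rewrite the Sample size section around one endpoint, one margin and one alpha with its sidedness. Delete the clause about a 19% increment in treatment success and the parenthetical 19% beside non-inferior. Keep the −10-point rule. Then take one of two routes:

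- **Proportion adherent.** State the power that the planned size delivers: about 29–34% with 82 per arm and 24–28% with 66, at true rates of 70–77.9%.
- **Mean percentage of days adherent.** Declare this as the sizing scale, consistent with Adherence assessment, and give the assumed SD with its source. Ninety percent power needs an SD of at most 17.7 points with 66 per arm or 19.8 with 82. If the supported SD is larger, state the resulting power.

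On either route, say whether 164 includes the 20% loss and how replacement of withdrawn participants bears on it. The cost is protocol and analysis-plan wording. No extra enrolment is asked for, which matters because Trial status reports enrolment at 70%. The drawback is that the stated power may be less favourable.

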### Recruitment

In order to enrol the required sample size in the stipulated time frame of the study, we shall enrol from sites with high volume numbers of MDR-TB in the country, which include Mulago National Referral Hospital and Lira Regional Referral Hospital. We shall also endeavour to enrol all eligible participants at each clinic day at both sites.

#### Randomization and allocation of intervention

Blinded randomization will be performed by the study team (medical officer or study nurse) at the time of enrolment using an automated randomization sequence within the Redcap data capture tool. The randomization will be done in real time on the Redcap tool as it will be Internet enabled. Participants will be randomized to either intervention arm (arm 1; self-administered therapy) or control arm (arm 2; DOT). Stratified randomization will be performed according to age group and gender. Due to the nature of the intervention and organization of patient care, it will not be possible to blind either participants or study staff to the study arm allocation

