**Methods:**

We plan to enrol 164 newly diagnosed MDR-TB patients aged ≥ 8 years from three regional hospitals based in rural and urban Uganda. Patients with conditions that affect their dexterity and ability to operate the MEMS-operated medicine equipment will not be eligible to participate in the trial. Patients are randomized to either of the two study arms: self-administered therapy with adherence being monitored using MEMS technology (intervention arm) or health facility-based DOT (control arm) and will be followed up monthly. Adherence is measured by the number of days the medicine bottle is open to access medication as recorded by the MEMS software in the intervention arm and treatment complaint days as recorded in the TB treatment card in the control arm. The primary outcome is the comparison of adherence rates between the two study arms.

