#### Eligibility criteria

We shall enrol consented patients with newly diagnosed pulmonary MDR-TB and RR-TB patients aged ≥8 years, initiated on oral MDR-TB therapy (category 1 or 2). Patients with any condition that inhibits the use of the MEMS device, e.g. dexterity or debilitating arthritis, will be excluded from participation.

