### Allocation concealment mechanism

The designing of the randomization sequence within the Redcap tool was performed by a biostatistician who is blinded from the participant enrolment activities. The variables used to design the randomization sequence included gender and age group. At the stage of enrolment, the randomization is conducted in real time on the Internet-enabled Redcap tool by the member of the study team conducting the enrolment. The study team have no control over the randomization sequence.

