### Allocation implementation

The study team (medical officer and or study nurse) having determined participant eligibility enter the participant gender and age into the automated randomization sequence within the Redcap tool and click a button to determine study allocation and or study arm in real time.

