## Laboratory assessments

Blood sampling to measure the concentrations of bedaquiline and linezolid will be conducted on months 2, 8 and 11 of treatment. Drug intake on the days for blood sampling will be performed by DOT and blood samples taken off prior to drug intake and 1-h post-drug intake. The blood samples will be placed in cooler boxes and transported to the laboratory on dry ice for samples from Lira Hospital and in a cooler box for samples from Mulago Hospital, processed and stored at −4 to −80 °C. Pharmacokinetic analysis will be performed at the Infectious Diseases Institution (IDI) translation laboratory. Quantification of the drug concentrations will be performed in batches using validated high-performance liquid chromatography (HPLC) and mass spectrometry at the Translation Laboratory of the Infectious Diseases Institute, Makerere University using MS.

Sputum smears and cultures will be performed as part of routine care and testing conducted at the government reference laboratory.

The study follow-up duration will be 24 months to cater for patients on both short- and long-term oral MDR-TB therapy. Treatment duration will be approximately 9 to 18 months: 9 months for participants that qualify for shorter MDR-TB/RR-TB treatment regimen and 18 months for those selected for the longer MDR-TB/RR-TB treatment regimen.

To ensure data quality, study information is captured with an e-questionnaire in Redcap that has been designed to send real-time notifications for inputted variables that may be out of range. The tool also does not accept for the person collecting data (medical officer and or study nurse) to verify the tool, but is redirected to the study coordinator and Data Manager to do the final verification for correct and missing data. In addition, the entire study team was trained afore on the use of the study Redcap tool and on other study-related standard operating procedure manuals including the collection of blood specimens for continued reference. In the event of a protocol violation, retraining on study protocol and procedures will be conducted.

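### Allocation is stratified by age group and gender only, and no covariates are named for the adherence comparison, so the non-inferiority interval may be slightly wider than it need be

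*Protocol article*

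**What the plan says.** **Allocation.** Under Randomization and allocation of intervention, "Stratified randomization will be performed according to age group and gender". Allocation concealment mechanism repeats the two factors: "The variables used to design the randomization sequence included gender and age group". Allocation implementation has staff "enter the participant gender and age into the automated randomization sequence within the Redcap tool". No section names site or regimen as a stratification factor.

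**Sites and regimens.** The Abstract says patients come "from three regional hospitals based in rural and urban Uganda", and Trial design says "from 3 TB tertiary care centres from 2 regions of the country". Study setting and Recruitment name only two hospitals. Eligibility criteria admit both regimen categories, and Laboratory assessments gives the durations as "9 months for participants that qualify for shorter MDR-TB/RR-TB treatment regimen and 18 months for those selected for the longer" regimen.

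**Analysis.** Under Adherence assessment, "The chi-square test and 1-way analysis of variance models will be used to compare outcomes by randomization arm". The same section adds an independent-samples t-test on mean adherence and an intention-to-treat GEE with identity link, exchangeable correlation and robust variance. It names no covariates. Secondary outcomes repeats the GEE and promises adjusted coefficients with 95% intervals. Additional analyses and handling of missing data plans multiple imputation of missing covariates for the primary analysis.

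**Decision rule.** Sample size declares non-inferiority if the lower 95% limit for MEMS minus DOT lies above −10%. It does not tie that limit to any one of the listed analyses.

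**The concern.** When randomisation is stratified, the strata normally enter the analysis. Stratifying holds the arms alike on age group and gender, but an unadjusted standard error takes no credit for that, so the interval tends to be too wide if those factors predict adherence.

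Site and regimen are plausible predictors too. The Background attributes low success under DOT to distance, roads, the cost of daily visits and overburdened facilities, which may differ between regions. Adherence is computed over the whole treatment period, so regimen sets its denominator. Both factors are known at enrolment, and neither is balanced by design.

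What is at stake is precision and clarity. In a non-inferiority trial an unnecessarily wide interval counts against the new strategy. And where several tests are listed, some unadjusted and one perhaps adjusted, the limit that decides the trial should come from one named model.

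**Working it through.** The article gives no figure on this point to reproduce, so the check asks what omitting such a factor costs.

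**Inputs from the article:** 82 per arm, 70% adherence, margin 10 points, 95% interval (Sample size). **Assumed, because not given:** the share q of patients at one level of a two-level factor, and the adherence gap D between its levels.

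**1. Size of chance imbalance.** The SD of the between-arm difference in share is √(2q(1−q)/82).
- q = 0.5: √(0.5/82) = 7.8 points; 95% range 1.96 × 7.8 = ±15.3 points.
- q = 0.3: √(0.42/82) = 7.2 points; 95% range ±14.0 points.

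**2. Effect on the estimate.** Shift = imbalance × D. With q = 0.5:
- D = 10: 0.8 points at one SD, 1.5 at the 95% limit.
- D = 20: 1.6 points at one SD, 3.1 at the 95% limit.

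**3. Is this already in the interval?** For a binary outcome at 70% in both arms, the SE of the difference is √(2 × 0.7 × 0.3/82) = 7.16 points, a half-width of 14.0 points. That SE already contains the shift as one variance component. Removing it at D = 20 gives √(7.16² − 1.56²) = 6.98 points. At D = 10 it gives √(7.16² − 0.78²) = 7.11 points.

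**4. Simulation** (100,000 trials, 82 per arm, q = 0.5, unadjusted against stratum-adjusted difference):

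| Gap D | SD of arm difference, unadjusted → adjusted | Chance of showing non-inferiority, arms equal |
|---|---|---|
| 10 | 7.17 → 7.15 | 29.5% → 29.7% |
| 20 | 7.16 → 7.01 | 29.5% → 30.7% |
| 30 | 7.17 → 6.79 | 29.4% → 32.0% |

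With a true difference of −10 points, non-inferiority is falsely declared in about 2.6% of trials unadjusted and 2.6–2.7% adjusted. The average estimate is −10 points throughout, so there is no bias.

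**5. Mean adherence.** The article also compares mean rates. Assume a between-patient SD of 20 points and an even split.
- Unadjusted SE: 20 × √(2/82) = 3.1 points.
- D = 20: the factor explains 0.25 × 20² = 100 of 400, or 25% of the variance. The SE becomes 3.1 × √0.75 = 2.7, about 13% narrower.
- D = 10: 25/400 = 6.25% of the variance, about 3% narrower.
- With an SD of 30 points instead, the gains are about 6% (D = 20) and 1% (D = 10).

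**The case against.** The strongest reply is that the covariate list belongs in a statistical analysis plan that is not shown, and that this is a condensed article. That largely stands. Adjusted coefficients are promised and covariates are foreseen for the primary analysis, so a reader who infers that the comparison ignores site and regimen goes too far. The article neither includes nor excludes them. What remains is that every test it does spell out is unadjusted, and that the analysis behind the −10% limit is not identified.

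A second reply is that few strata are a defensible choice. Assuming two age groups, crossing age, gender, three sites and two regimens gives 2 × 2 × 3 × 2 = 24 cells for 164 patients, about seven each. That also stands, and it is why the remedy lies in the analysis.

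A third is that the links to adherence are loose. DOT is given at a peripheral facility near home, so the enrolling hospital is only a rough proxy for distance or facility load. Adherence is a proportion, so a longer window does not by itself move it. Both points are fair. The article does not show that site and regimen are the factors that most affect delivery, and that should not be claimed.

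**Conclusion.** The point holds as a minor matter of precision and prespecification. Adjustment would narrow the interval a little: under 1% to about 2% in SD for a binary outcome with 10- to 20-point gaps, and about 1% to 13% for mean adherence with between-patient SDs of 20 to 30 points. These figures rest on an even split and on gaps that the article does not give. They cover one factor at a time.

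A reader might infer from step 2 that chance imbalance can use up about a third of the 10-point margin. The article does not support that. A shift of 3.1 points needs an assumed 20-point gap, a near-even split and the 95% extreme. At that gap, a shift of 3.3 points or more in either direction has about a 3.5% chance, and half of those favour MEMS. More fundamentally, chance imbalance under randomisation is already inside the standard error and the interval, so it takes nothing further from the margin. The false-positive rate is the same with or without adjustment.

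Nor does adjustment cure low power: with a binary outcome at 70% in both arms, the chance of showing non-inferiority stays near 30%.

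**What to change.** Leave the allocation list unchanged; Trial status reports enrolment at 70%. In Adherence assessment, state that the non-inferiority limit is read from the identity-link GEE with these prespecified fixed covariates: age group and gender as used in the randomisation, enrolling site, and regimen category recorded at enrolment. Keep the chi-square, analysis of variance and t-test results as supportive.

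Two details go with this. Define site, because the Abstract and Trial design count three centres while Study setting and Recruitment name two hospitals. And fix the covariate list before adherence is compared by arm, including at the interim analysis, because the study team and data manager are not blinded.

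The cost is a sentence or two and a few degrees of freedom. All four variables are known at enrolment, so no new data are needed.

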#### Secondary outcomes

To assess correlation of specific MDR-TB drug serum concentrations with observed adherence, bedaquiline and linezolid pre-dose concentrations (C_trough_) will be used. To cater for those who may be adherent but have low bedaquiline or linezolid concentrations, we will use of cut-off value of bedaquiline C_trough_ from previous studies, below which a participant will be classified as non-adherence. Linezolid will be used to assess more recent adherence than bedaquiline.

We will compare time to sputum culture conversion in the intervention and control arm using time to event analysis. We shall also use chi-square testing to compare treatment success rates in the intervention and control arms. Treatment success will be evaluated using a composite outcome that includes TB cure (for microbiologically diagnosed patients) and TB treatment completion (for clinically diagnosed TB). We will undertake per-protocol and intention to treat analyses to compare TB cure rates in the two study arms. We will determine the proportions of patients retained in care of retention in care at 2 and 6 months in the two study arms using chi-square tests. Study outcomes by randomization arm will be compared using a generalized estimating equations (GEE) model using repeated measures with identity link, exchangeable correlation structure and robust variance estimates. Adjusted coefficients along with their corresponding 95% CIs will be generated. Statistical significance will be set at the *P* < .05 level and statistical analyses performed using Stata version 14 (StataCorp, College Station, TX, USA).

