#### Additional analyses and handling of missing data

Interim data analysis will be conducted once 50% of the overall sample size has been achieved with the purpose of guiding the data monitoring board on recommendations for the study. Missing data will be dealt with as missing covariate and outcome data. As a generalized estimating equations model will be used, missing outcome data will be dealt with using a missing at random assumption. If > 3% of data for covariate data is missing, multiple imputation will be used for the primary analysis. Given the way the adherence rate is computed, we anticipate that there may be a number of ways that the outcome measure could be missing. These include loss to follow-up and or partial information collected at anyone study visit. A further analysis will be performed in which missing primary outcome data will be imputed. Multiple imputation will be also performed on missing covariate and outcome data for all secondary clinical analyses in a similar way to that performed for the primary analysis.

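### Randomisation is stratified by age group and gender, but no stated adherence analysis is said to use these strata, and the analysis that supplies the deciding 95% CI is not named

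*Protocol article*

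**What the plan says.** Three sections of the protocol article describe the stratification. Randomization and allocation of intervention states: "Stratified randomization will be performed according to age group and gender". Allocation concealment mechanism repeats it: "The variables used to design the randomization sequence included gender and age group". Allocation implementation shows it in use, since staff "enter the participant gender and age into the automated randomization sequence within the Redcap tool". No block size or other method of balancing within strata is described.

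Adherence assessment names several analyses of adherence:
- a chi-square test and one-way ANOVA to set the two groups against each other;
- for mean adherence, a two-group test: "We shall use independent samples *t*-test to test for statistical difference mean adherence rates in the patient in the intervention and control arms";
- for the intent-to-treat comparison, a "generalized estimating equations model using repeated measures with identity link, exchangeable correlation structure and robust variance estimates", with no covariates listed.

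Two later sections touch on adjustment. Secondary outcomes names the same GEE for study outcomes by arm and adds: "Adjusted coefficients along with their corresponding 95% CIs will be generated". Additional analyses and handling of missing data says: "If > 3% of data for covariate data is missing, multiple imputation will be used for the primary analysis". Neither says what the covariates are.

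Sample size sets the decision rule: the lower 95% limit of MEMS minus DOT must lie above −10%. It does not say which analysis produces that interval.

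**The concern.** When a design balances the arms on factors that predict the outcome, variation between strata is largely removed from the arm difference. An analysis that omits those factors still counts that variation as error, so its standard error is larger than it need be. The usual remedy is to carry the stratification factors into the analysis.

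Here three of the named analyses cannot do that as described, and the fourth is silent on it. The non-inferiority verdict turns on a single confidence limit in a trial of 82 per arm. Adjusted and unadjusted analyses can give different limits, and the article leaves open which one counts. At stake are a small amount of power and a choice that is better closed before results are known.

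**Working it through.** **The plan's own figure.** The article gives no figure for the effect of the strata. Its sample size, 164 (82 per arm), does not follow from the inputs as stated:
- Reading the 19% increment as 70% against 89%, two-sided 5% and 90% power need 93 per arm, or 93/0.8 → 117 after 20% loss.
- Non-inferiority with 70% in both arms and a 10-point margin needs (1.96 + 1.2816)² × 2 × 0.70 × 0.30 / 0.10² ≈ 442 per arm, or 442/0.8 → 553 after loss.
- 82 per arm appears only if an input is changed, for example 70% against 90%, one-sided 5%, unpooled variance: 65 per arm, then 65/0.8 → 82.

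That is a separate matter. It is given here because it sets the scale for what follows.

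**Inputs from the article.** 82 per arm; about 82 × 0.8 = 65.6 evaluable after 20% loss; adherence 70%; margin 10 points; 95% CI.

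**Assumptions.** Adherence analysed as a proportion of patients, 70% in both arms (no separate DOT rate is given); true difference 0; strata balanced by design and explaining a share R² of the outcome variance. The documents give no R², so a range is shown.

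**Formulas.**
- Unadjusted SE = √(2 × 0.70 × 0.30 / n). At n = 82 this is 0.0716, so the half-width is 1.96 × 0.0716 = 14.0 points.
- Adjusted SE = SE × √(1 − R²).
- Power, unadjusted = Φ((0.10 − 1.96 × SE) / adjusted SE).
- Power, adjusted = Φ(0.10 / adjusted SE − 1.96).
- One-sided error of the unadjusted interval = Φ(−1.96 / √(1 − R²)).

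| R² (assumed) | Adjusted half-width, n = 82 | Power unadj. / adj., n = 82 | Power unadj. / adj., n = 65.6 | One-sided error, unadj. |
|---|---|---|---|---|
| 0 | 14.0 | 28.7 / 28.7% | 23.9 / 23.9% | 2.50% |
| 2% | 13.9 | 28.5 / 29.2% | 23.7 / 24.3% | 2.39% |
| 5% | 13.7 | 28.2 / 29.9% | 23.3 / 24.9% | 2.22% |
| 10% | 13.3 | 27.7 / 31.3% | 22.7 / 26.0% | 1.94% |

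The gain from adjusting is 1.6 to 1.7 points at R² = 5% and 3.3 to 3.6 points at 10%.

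**How large is a given R²?** With two equal groups, R² = (gap/2)² / (0.70 × 0.30). A 10-point gender gap (65% against 75%) gives 0.0025/0.21 = 1.2%. A 20-point gap (60% against 80%) gives 0.01/0.21 = 4.8%.

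**Without balancing within strata.** The unadjusted interval then has its nominal level and its power is the R² = 0 figure, 28.7% at n = 82. Adjusting would raise this to about 29.9% at R² = 5% and 31.3% at 10%, a gain of 1.2 and 2.6 points.

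**If adherence is analysed as a mean.** No SD is given. A simulation with an assumed SD of 20 points, about 64 per arm, four equal strata and true difference 0 gave power of 0.81 unadjusted against 0.82 adjusted at R² = 5%, and 0.82 against 0.85 at 10%. The half-width was 7.0 points unadjusted, against 6.8 and 6.6 adjusted. Overall power depends heavily on the outcome scale and the SD; the gain from adjusting stays small.

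**The case against.** The strongest reply is that the article already foresees adjustment. It names a GEE for the intent-to-treat comparison, promises adjusted coefficients with 95% CIs, and plans imputation of missing covariates for the primary analysis, which makes sense only if that analysis has covariates. Which covariates enter a model is commonly left to a full protocol or SAP, and those are not shown.

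Much of this stands. Adjustment for age group and gender is neither stated nor excluded, and a missing covariate list alone would be no finding. What it does not answer is that the article itself names three tests that ignore the strata, one of them assigned to mean adherence, and does not rank them against the GEE. The sentence on adjusted coefficients also sits under Secondary outcomes.

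A reader might infer more: that the deciding interval is too wide and that its error rates are off their nominal level. The documents do not support this. No section ties the −10% rule to an unadjusted test. The article gives no figure for how far age group or gender predicts adherence. No balancing method within strata is described, and without one the unadjusted interval keeps its nominal coverage.

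The direction is also safe. Any departure makes non-inferiority harder to claim, so false claims do not become more likely.

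**Conclusion.** The point holds in a limited form. The design stratifies on two factors, no named analysis is said to use them, and the analysis behind the deciding CI is not identified. Whether power is actually lost depends on three conditions that the article leaves open: that an unadjusted test decides, that the strata are prognostic, and that allocation is balanced within them. If all three hold, the interval is mildly conservative and the loss is 0 to about 2 percentage points of power for R² up to 5%, and 3 to 4 points at 10%. If only the balancing is absent, coverage is correct and some efficiency is lost. These sizes rest on assumed R² values and, on the mean scale, an assumed SD.

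This is a worthwhile clarification of modest size. It should not be read as a remedy for the trial's power: at 70% adherence in both arms, power against the −10% margin is about 24 to 29% with or without the strata.

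**What to change.** In Adherence assessment, state that the MEMS minus DOT difference and the 95% CI judged against −10% come from the identity-link GEE already named, with arm, age group and gender as main effects, using the values entered at randomisation. For adherence as a binary outcome, replace the plain chi-square by a Mantel-Haenszel risk difference with its 95% CI over the same strata. Label the remaining unadjusted tests as supportive or drop them.

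The cost is a sentence or two. Both variables are entered for every participant at randomisation, so no new data are needed. Entering them as main effects in the GEE, without interactions, limits the harm that a small stratum of 8–17-year-olds could do. The gap between 164 patients and the −10% margin has to be dealt with separately.
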